### Criteria for discontinuing or modifying allocated interventions {11b}

Participants can leave the trial at any time for any reason if they wish to do so without any consequences. The participant’s participation in this trial can also be ended by the investigator if the participant is uncooperative and/or does not attend study visits. The participant’s data that have been collected up to that moment will be included in the analysis. This trial will be prematurely ended in case of any abundance in adverse events or procedure/compound-related complications or if the independent physician advises this termination. Criteria for trial termination include any suspected unexpected serious adverse event (SAE) based on an allergic reaction and clear allergic or iatrogenic effects in two or more participants.

### Strategies to improve adherence to interventions {11c}

In this trial, improving adherence to interventions will be through face-to-face reminders at the initial study drug dispensing and each follow-up thereafter. The reminders to participants include the following: (1) the importance of following study guidelines for adherence to take study drugs; (2) instructions about taking study drugs including dose timing, storage, and importance of taking study drugs whole, and what to do in the event of a missed dose; (3) notification that there will be a study drug count at every follow-up visit. Participants will return the unused study drugs and bottle at each follow-up visit. At the same time, unused study drugs will be counted and recorded in the CRF by investigators; (4) importance of calling the investigators if experiencing problems possibly related to study drugs such as symptoms, lost study drugs.

### Relevant concomitant care permitted or prohibited during the trial {11d}

During the trial, the use of drugs with the same effect as aspirin or lumbrokinase is prohibited.

### Provisions for post-trial care {30}

There is no ancillary or post-trial care. The trial has insurance, which is in accordance with the legal requirements in China. This insurance provides coverage for damage to participants through injury or death caused by any activities of the trial. The insurance applies to the damage that becomes apparent during the trial.

### Outcomes {12}

The primary outcome is the Modified Rankin Scale (mRS) score.

The secondary outcomes are National Institutes of Health Stroke Scale (NIHSS) score, Activity of Daily Living (ADL) Scale score (Barthel index), coagulation function: prothrombin time (PT), activated partial thromboplastin time (APTT), serum fibrinogen (FIB) concentration, and serum hypersensitive C-reactive protein (hs-CRP).

The safety outcomes are liver function and kidney function: alanine aminotransferase (ALT), aspartate aminotransferase (AST), total bilirubin (TBil), blood urea nitrogen (BUN), serum creatinine (Scr), and urine protein (R-PRO), as well as serum fibrinogen (FIB), occurrence of adverse events (AEs) and serious adverse events (SAEs), and occurrence of bleeding events. Adherence of participants will also be assessed.

The exploratory outcomes include fasting lipid panel: total cholesterol (TC), triglyceride (TG), high-density lipoprotein (HDL), low-density lipoprotein (LDL), and recurrence rate (incidence of ischemic stroke events), occurrence of cardiovascular and cerebrovascular events, and mortality rate. A study schedule and evaluation of outcomes are provided in Table 1.

The five elements of the primary outcome and secondary outcomes are specified in Table 2: the domain, specific measurement, specific metric, method of aggregation, and time point.

**Table 2 Tab2:** Five elements of outcomes

	Domain	Specific measurement	Specific metric	Method of aggregation	Time point
Primary outcome	The Modified Rankin Scale (mRS) score	The Modified Rankin Scale (mRS) score	Change from baseline to 14, 28, 60, 90, and 180 days	Proportional-odds logistic-regression model	Baseline, 14, 28, 60, 90, and 180 days
Secondary outcome	National Institutes of Health Stroke Scale (NIHSS) score	National Institutes of Health Stroke Scale (NIHSS) score	Change from screening period to 14, 28, 60, and 90 days	Repeated-measures analysis model	Screening period, 14, 28, 60, and 90 days
	Activity of Daily Living (ADL) Scale score (Barthel index)	Activity of Daily Living (ADL) Scale score (Barthel index)	Change from baseline to 90 and 180 days	Repeated-measures analysis model	Baseline, 90 and 180 days
	Prothrombin time (PT)	Prothrombin time (PT)	Change from baseline to 14, 28, 60, and 90 days	Repeated-measures analysis model	Baseline, 14, 28, 60, and 90 days
	Activated partial thromboplastin time (APTT)	Activated partial thromboplastin time (APTT)	Change from baseline to 14, 28, 60, and 90 days	Repeated-measures analysis model	Baseline, 14, 28, 60, and 90 days
	Serum fibrinogen (FIB) concentration	Serum fibrinogen (FIB) concentration	Change from baseline to 14, 28, 60, and 90 days	Repeated-measures analysis model	Baseline, 14, 28, 60, and 90 days
	Serum hypersensitive C-reactive protein (hs-CRP)	Serum hypersensitive C-reactive protein (hs-CRP)	Change from baseline to 90 days	Repeated-measures analysis model	Baseline, 90 days

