### Sample size {14}

A sample size of 173 participants was calculated to provide 80% power to detect a common odds ratio (indicating the odds of improvement of 1 point on the mRS) of 6.02 in the distribution of scores on the mRS at 90 days between the treatment and control groups with a two-sided significance level of 0.05, assuming a similar between-group distribution of the mRS as in a recent AIS trial [11]. Taking into account of possible protocol violations and dropouts, we intend to enroll 220 participants (110 per group).

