## Statistical methods

### Statistical methods for primary and secondary outcomes {20a}

The primary outcome will be analyzed by fitting a proportional-odds logistic-regression model to calculate the common odds ratio as a measure of the likelihood that the treatment group will lead to lower mRS scores than the control group (shift analysis).

For secondary outcomes, categorical variables will be compared with chi-square test or Fisher exact test. Longitudinal continuous variables will be analyzed by fitting a repeated-measures analysis model. Additionally, adverse events, serious adverse events, and laboratory abnormalities will also be compared using the chi-square test or Fisher exact test as appropriate.

All analyses will be performed in the intention-to-treat population using SAS version 9.4 (SAS Institute Inc). *P* values of less than 0.05 will be considered statistical significance, and all tests will be two-sided. No adjustments will be made for multiple comparisons.

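### Table 2 sets the primary metric as change in mRS from day 0, while the sample size and the statistical methods use the mRS level

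*Protocol article*

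**What the plan says.** Outcomes {12} names the primary outcome simply as the mRS score ("The primary outcome is the Modified Rankin Scale (mRS) score"), then refers the reader to Table 2 for its five elements. In Table 2 the metric is "Change from baseline to 14, 28, 60, 90, and 180 days", the method of aggregation is "Proportional-odds logistic-regression model", and the time points are "Baseline, 14, 28, 60, 90, and 180 days".

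The statistical methods {20a} describe the common odds ratio as the likelihood that "the treatment group will lead to lower mRS scores than the control group (shift analysis". The sample size {14} places the target odds ratio "in the distribution of scores on the mRS at 90 days between the treatment and control groups".

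Table 1 has two mRS rows before treatment: the pre-stroke score at screening, and the mRS at D0. The baseline in Table 2 is therefore the acute D0 score. The eligibility limit of mRS 2 or less applies to the pre-stroke score and does not restrict D0.

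**The concern.** Table 2 describes a within-patient difference. The other two sections describe where patients stand on the scale. One proportional-odds model cannot be the primary analysis of both, and an analysis plan cannot follow all three statements.

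Two things are at stake. First, the common odds ratio changes meaning: for the level it is the odds of a better functional state, and for change it is the odds of a larger drop from a score taken during the acute stroke. Second, if the article leaves the metric open, the choice could be made after results are seen, and the two analyses can give different answers.

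**Working it through.** **1. The statements side by side**

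| Place | Variable | Visit |
|---|---|---|
| Outcomes {12}, Table 2 | Change in mRS from D0 | 14, 28, 60, 90 and 180 days |
| Statistical methods {20a} | mRS level, lower is better | Not named |
| Sample size {14} | mRS level | 90 days |

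The term shift analysis in {20a} does not rescue the change metric. There it means a shift of the score distribution between arms, not subtraction of a baseline.

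**2. The plan's own figure**

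The stated figure is 173 participants for 80% power, two-sided 0.05, common odds ratio 6.02. Whitehead's formula for 1:1 allocation is

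N = 12(z_a + z_b)² / [(ln OR)² (1 − Σp³)], where p are the average category proportions.

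With z_a = 1.960, z_b = 0.842 and ln 6.02 = 1.795, this is 94.2 / 3.222 = 29.2, divided by (1 − Σp³). The article does not give the mRS distribution, so five seven-level distributions were assumed. They give N = 31 to 43, so 173 is not reproduced even for the level. That is a separate matter. It is noted here only because the calculation, whatever its merits, is stated for the level at 90 days and not for change.

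**3. Ordering of survivors under change** (follow-up minus D0, lower is better; no assumption about death)

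- 5 to 3 is −2 and 2 to 1 is −1. The first ranks better, but the second patient ends in the better state.
- The same happens with D0 scores of 3 to 5 only: 5 to 3 (−2) ranks ahead of 3 to 2 (−1).
- 5 to 3, 4 to 2 and 3 to 1 all score −2 and are tied, although they end in three different states.

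**4. Ordering of deaths** (assumption: death = 6)

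A death scores 6 minus the D0 score: +1 from 5, +2 from 4, +3 from 3. Listing every combination of a death and a worsening survivor on the 0–6 scale:

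- All D0 scores 0 to 5: 20 strict inversions (death ranked better) and 15 ties.
- D0 scores 3 to 5 only: one inversion, 5 to 6 (+1) ahead of 3 to 5 (+2), and three ties (5 to 6 with 3 to 4; 5 to 6 with 4 to 5; 4 to 6 with 3 to 5).

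Analysed as the level at one visit, with death = 6, no inversion is possible.

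**5. How often inversions could occur** (illustration, assumed D0 distributions and baseline–outcome correlations)

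For a death with D0 mRS 5, a strict inversion needs a survivor who worsens by two or more grades; deaths from lower D0 scores need still greater worsening. Such survivors made up about 0.2% to 2.3% of patients across the simulations. Of 220 patients that is 0.002 × 220 = 0.4 to 0.023 × 220 = 5. In one set of runs, strictly inverted pairs were about 0.2% to 0.7% of all death–survivor pairs.

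**6. Power** (illustration, 86 per arm, odds ratio 2.2 given baseline, D0 mRS 2 to 5, rank test)

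Power was 0.61 to 0.83 for the level and 0.77 to 0.82 for change. Which was higher depended on how strongly baseline predicts outcome.

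**The case against.** The strongest reply is that the article mostly points to the level. The abstract, Objectives {7} and the text of Outcomes {12} name the score, and the sample size and methods sections both use it. Only one table cell says change, and every secondary row in Table 2 carries similar wording, so the cell may be template text. That is plausible, and the misordering is accordingly a consequence of following Table 2 literally, not a prediction of what will be done. It does not remove the conflict, because the article names Table 2 as the place where the outcome's elements are specified and gives no rule of precedence.

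One might also argue that {14} supports change, since it explains the odds ratio as improvement by one point. But the same sentence locates that odds ratio in the distribution of scores at 90 days between groups.

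A reader might infer more than the documents support:

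- *That many deaths would be counted as better than survival.* The article never says how death is scored on the mRS and lists mortality separately as an exploratory outcome. Even with death = 6, entry at NIHSS 6 to 14 makes low D0 scores less likely, and inversions are rare (steps 4 and 5).
- *That proportional odds would fail.* In an illustration with a common odds ratio of 2.2 on the level, cumulative odds ratios for change ran from about 2.1 to 2.7. That is a mild departure and depends on assumed distributions.
- *That change costs power.* Step 6 shows that it can go either way.
- *That change is no ordinal outcome at all.* It is ordered, but its order is not that of functional state. Under randomisation it still gives a valid test of no effect if fixed in advance.

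**Conclusion.** The concern holds as an internal contradiction about the sole primary outcome: Table 2 specifies change from the acute D0 score, and {14} and {20a} specify the level. These are different endpoints with differently defined odds ratios, and the article does not settle which is primary.

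The misordering among survivors follows from arithmetic alone. The misordering of deaths depends on coding death as 6 and would be uncommon: the survivors it requires were about 0.2% to 2.3% of patients under assumed distributions. No figure for lost power, bias or altered sample size follows from the article. The conclusion needs none of them. It rests on the conflicting statements and on the fact that a change score does not rank patients by functional state.

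**What to change.** In Table 2, replace the primary metric by the mRS level at day 90, the visit used in {14}, analysed by the proportional-odds shift model of {20a}. State in the same place how death is scored, for example as the worst category. If baseline adjustment is wanted, enter D0 mRS as a covariate and do not subtract it. Naming day 90 also settles which of the five listed visits is primary. That is a separate question, but the same edit answers it.

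The cost is one table cell and one sentence. Visits and data collection are unchanged. The trial status section reports 46 of 220 participants recruited on 29 November 2021, and {18a} places database lock after all 180-day visits, so on the article's own timeline the correction can be made and dated well before unblinding.

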### Participant timeline {13}

Participant timeline is shown in Table 1.

### Sample size {14}

A sample size of 173 participants was calculated to provide 80% power to detect a common odds ratio (indicating the odds of improvement of 1 point on the mRS) of 6.02 in the distribution of scores on the mRS at 90 days between the treatment and control groups with a two-sided significance level of 0.05, assuming a similar between-group distribution of the mRS as in a recent AIS trial [11]. Taking into account of possible protocol violations and dropouts, we intend to enroll 220 participants (110 per group).

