### Trial design {8}

In this prospective, multicenter, randomized, double-blind, placebo-controlled clinical trial, lumbrokinase plus aspirin is compared to aspirin alone. We plan to enroll 220 participants with first time diagnosis of AIS. The participant allocation ratio is 1:1. Participants will be treated for the first 90 days. Then, all participants will be treated with aspirin only and followed up for another 90 days (180-day follow-up). A flowchart of the study is shown in Fig. 2. Central ethical approval of LUCENT has been confirmed by the Ethics Committee of Dongzhimen Hospital, Beijing University of Chinese Medicine (No.DZMEC-KY-2019-202). This trial will be conducted in adherence to the Declaration of Helsinki. Informed consent will be obtained from all participants or their legal representative, in writing, before inclusion in the trial. The trial has been registered in the Chinese Clinical Trial Registry (ChiCTR2000032952).

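### The stated common odds ratio of 6.02, 80% power and 173 participants cannot be reproduced together under any credible 90-day mRS distribution

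*Protocol article*

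**What the plan says.** All the planning figures stand in Sample size {14} of the protocol article:

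- Size and power: "A sample size of 173 participants was calculated to provide 80% power".
- Effect: a "common odds ratio (indicating the odds of improvement of 1 point on the mRS) of 6.02 in the distribution of scores", compared "in the distribution of scores on the mRS at 90 days between the treatment and control groups".
- Error rate: "with a two-sided significance level of 0.05".
- Outcome distribution: "assuming a similar between-group distribution of the mRS as in a recent AIS trial". The distribution itself is not printed.
- Enrolment: 220 (110 per group), to allow for protocol violations and dropouts.

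Trial design {8} adds that "The participant allocation ratio is 1:1". Statistical methods {20a} names a proportional-odds logistic regression (shift analysis) for the primary outcome, so the planned test and the planning effect are on the same scale. The article gives no other ground for 173, such as a safety target or a second endpoint.

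**The concern.** An odds ratio of 6.02 across the whole mRS is a very large effect, and very large effects need few participants. A total of 173 at only 80% power looks several times too many for it.

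This statement is the only justification given for the size of the trial, and its effect is the yardstick for reading the result. A reader told that the trial was built to see a six-fold shift would take a common odds ratio of 2 to be far below the design's reach. In fact, 173 participants have well over half the power needed to detect it. If 6.02 was truly intended, the trial is several times larger than that effect requires. If 173 is right, the published effect is wrong.

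**Working it through.** **Inputs from the article.** Common odds ratio 6.02, power 80%, two-sided alpha 0.05, 1:1 allocation, 173 in total, proportional-odds model. **Assumed:** the control mRS distribution, which is not printed and is therefore varied below.

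**Formula (Whitehead, ordinal outcome, 1:1).** N = 12(z₀.₉₇₅ + z₀.₈₀)² / [(ln OR)² · f]. Here f = 1 − Σp̄ᵢ³, and p̄ᵢ is the share in grade i averaged over the two arms.

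**Step 1: try to reproduce 173.**
- 12(1.960 + 0.842)² = 94.19.
- ln 6.02 = 1.795, squared 3.222.
- Since f cannot exceed 1, the smallest N is 94.19/3.222 = 29.2.

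The first two result columns give f and N at OR 6.02. The last three describe N = 173, with f recomputed at each odds ratio.

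| Assumed control shares, mRS 0 to 6 (%) | f at 6.02 | N at 6.02 | OR with 80% power | Power at OR 2.0 | Power at OR 1.5 |
|---|---|---|---|---|---|
| equal sevenths | 0.956 | 30.6 | 2.11 | 74% | 33% |
| 15, 25, 20, 15, 12, 5, 8 | 0.939 | 31.1 | 2.12 | 73% | 33% |
| 8, 17, 17, 16, 20, 10, 12 | 0.967 | 30.2 | 2.11 | 74% | 33% |
| 3, 7, 10, 15, 25, 18, 22 | 0.977 | 29.9 | 2.12 | 74% | 33% |
| 30, 30, 15, 10, 8, 3, 4 | 0.852 | 34.3 | 2.16 | 71% | 32% |
| 10, 60, 10, 8, 6, 3, 3 | 0.802 | 36.4 | 2.33 | 63% | 27% |
| 60, 15, 10, 6, 4, 2, 3 | 0.577 | 50.7 | 2.47 | 59% | 26% |

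The figure of 173 is not reproduced in any row.

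**Step 2: check the formula by simulation.** The formula is a large-sample one and the effect is large. Simulated Wilcoxon tests (3,000 trials per setting) place 80% power at about 33 to 44 participants for the first six rows. For the last row, power was 73% at 52 and 80% at 60. The formula is therefore somewhat optimistic, but the gap to 173 remains.

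**Step 3: power of 173 at OR 6.02.** Power = Φ(√[N(ln OR)² f/12] − 1.960). In the least favourable row, √(173 × 3.222 × 0.577/12) = √26.8 = 5.18, and Φ(5.18 − 1.96) = 0.9993. All other rows are higher.

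**Step 4: what would make 173 right.** f would have to be 94.19/(3.222 × 173) = 0.169. With two occupied grades, 1 − x³ − (1 − x)³ = 0.169 gives x = 0.94. That means about 94% of all participants in one grade, for example 90% of controls and 98% of treated. This is not credible on a seven-grade scale for patients entered with NIHSS above 5 and below 15 (Eligibility criteria {10}).

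**Step 5: what 173 does detect.** OR = exp√[94.19/(173 f)]. For equal sevenths, f at the solution is 0.977, so √(94.19/169.0) = 0.747 and exp(0.747) = 2.11. For the last row, f is 0.666, which gives 2.47.

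**Step 6: other readings.**
- For the first six rows, one-sided alpha gives 24–29 and 90% power gives 40–49.
- Misprints of 6.02 do not recover 173. The nearest one tried, 2.06, gives 185–238 over the first six rows, and ln OR = 0.602 gives 266–343.
- A dichotomised mRS at OR 6.02 gives 42–84 for control rates of 10–70%, 128 at 80% and 258 at 90%.

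**The case against.** The strongest reply is that the calculation rests on an mRS distribution in a cited trial that is not reproduced, so an outside check cannot prove an error. A reader might infer from the mismatch that the statement is internally impossible. That goes too far, because 173 can be reached with extreme concentration in one grade. What stands is that no credible distribution reaches it.

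A second reply is that another method may have been used. The article glosses the odds ratio as one-point improvement, and Table 2 gives the metric as change from baseline. If a binary improved-or-not endpoint was powered, a two-proportion formula at OR 6.02 gives about 170 in total for an assumed control rate of 85% (97% on treatment). The wording about a common odds ratio over the distribution of scores argues against this. Still, the fault could lie in the description of the method rather than in either number.

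A reader might also infer that the trial's real target is an odds ratio of about 2.2. The documents do not support this. The article names one effect, 6.02, and any value near 2.2 is solved backwards on the assumption that 173 is right.

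Finally, it can be said that 173 is more than enough for the stated effect and that 6.02 plays no part in the primary analysis. Both are true. Neither makes the stated power belong to the stated effect.

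**Conclusion.** The statement is wrong as written. Under the planned proportional-odds analysis, an odds ratio of 6.02 needs roughly 30 to 45 participants for 80% power. With 60% of controls in the best grade it needs about 50 by formula, or about 60 by simulation. The stated 173 is therefore about three to five times too many for that effect.

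The mismatch is robust to every ordinary mRS distribution tried. The exact reverse figures are less firm: the detectable odds ratio of 2.1–2.5 and the power at 2.0 and 1.5 rest on assumed control distributions and on proportional odds. The article does not show whether the odds ratio, the number or the method description is at fault. Nor does it show that the trial is too small, because it names no effect smaller than 6.02.

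**What to change.** Redo the calculation from the 90-day mRS distribution of the cited trial. State that distribution and the formula or software method, and correct whichever of the odds ratio, the sample size or the method description proves wrong.

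If 173 evaluable and 220 enrolled are kept, replace 6.02 with the common odds ratio that 173 detects with 80% power (about 2.1–2.5, depending on the distribution). Give the power at smaller values such as 2.0 and 1.5, and say that the effect was restated after the size had been fixed.

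The cost is one recalculation and a corrected paragraph. It cannot be promised in advance that the number stays the same: if the recalculation starts from an intended effect other than 6.02, the required size may change.
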